## 11) DATA MANAGEMENT

Participants in the mobile app group will use unique, coded credentials to log in to the study app. For each participant, we will generate a random ID code (a random alphanumeric string) and password. During the initial login, participants will have the option to use their phone's built-in biometric identification features (fingerprint or face ID) to log into the app in the future. All research data collected by the app will be encrypted on the device, and the participant will not be able to access or read the encrypted data using their credentials. We will not have access to the biometric signatures used by the smartphone operating systems.

Periodically, when a network connection is available, the app will upload data to an encrypted server using an encrypted (and HIPAA compliant) transmission protocol. As part of the upload process, the data will be validated as uncorrupted, then deleted from the phone. Research data stored on the encrypted server will be coded using the participant's random alphanumeric ID code, and it will not be directly linked to personally identifiable information (PII) during data storage or analysis, except insofar as geolocation data may itself contain identifying information. Access to the encrypted and coded data stored on the server will be password-protected, and it will only be accessible to authorized, human subjects trained, personnel within Datacubed Health. Data will be maintained on the server for the duration of the study. The data will only be analyzed in a coded or de-identified form. De-identification in this case refers to the removal of ID codes.

Participants in the web groups will use unique, coded credentials to log in to the web platforms. For each participant, we will generate a random ID code (a random alphanumeric string) and password. All research data collected by the web platforms will be encrypted, and the participant will not be able to access or read the encrypted data using their credentials.

Each participant in the paper group will be assigned a random ID code (a random alphanumeric string) which will be used to identify his/her data when the paper surveys are transcribed into electronic format for data analysis.

Ongoing quality assurance checks will be performed throughout the study, to identify any invalid or missing data and to address the possible reasons for such problems.

### **Data analysis plan:**

Once data collection is complete for all participants, we plan to perform independent t-tests on the outcome measures of retention and compliance and a 1-way ANOVA on the outcome measure(s) of engagement. See Section 8 for a description of how each measure will be calculated.

### **Aim 1: Test whether electronic administration influences participant retention and compliance**

To test whether electronic administration influences participant retention and compliance, we will perform a one-way analysis of variance (ANOVA) with Dunnett's test for multiple comparisons to assess retention and compliance between the groups receiving paper-based administration of surveys and the two groups receiving electronic administration on the non-gamified websites. Non-parametric alternatives (e.g., Kruskal-Wallis test) may be used in place of ANOVA if the data significantly violate the assumptions for ANOVA. This approach will eliminate the potential confounding effect of gamification on the outcome measures by excluding the group receiving electronic administration of the gamified mobile app.

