**Aim 1: Test whether electronic administration influences participant retention and compliance**

Hypothesis: There will be a significant difference in retention and compliance between paper and electronic (web) administration of surveys. Retention will be measured by the number of days from the first assigned instrument to the date of the last fully completed instrument and compliance will be measured by the number of fully completed instruments. Electronic administration will improve retention and compliance, such that administration on paper will have lower retention and compliance compared to electronic administration on the non-gamified websites (Datacubed Health website and third-party website).

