**Aim 2: Test whether gamification influences participant retention and compliance**

Hypothesis: There will be a significant difference in retention and compliance between gamified and non-gamified electronic administration of surveys. Gamification will improve retention and compliance, such that administration on the gamified app will have higher retention and compliance compared to administration on the non-gamified websites (Datacubed Health website and third-party website).

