**Aim 3: Test whether the format of survey administration influences the self-reported usability of the survey format**

Hypothesis: There will be a main effect of the format of survey administration on self-reported usability of the survey format. Usability will be derived from a self-report usability survey that assesses the ease of use and pleasantness of the survey format; an overall measure of usability as well as different factors of usability will be derived from the survey responses.

Administration on paper will result in the lowest usability, and electronic administration on the gamified mobile app will result in the highest usability. Electronic administration on the non-gamified websites will result in intermediate usability, with use of Datacubed Health's website resulting in usability equivalent to or superior to a third-party website (i.e., paper < third-party website < Datacubed Health website < mobile app).

**Aim 4: Test whether payment schedule influences retention and compliance differently by format of instrument administration.**

Hypothesis: There will be a significant difference in retention and compliance between participants who receive biweekly payments and participants who receive one payment, adding up to the same amount, at study end. All participants will receive \$5.00 for each completed survey. Participants who receive payment at study end will show reduced retention and compliance, and this will vary by format of survey administration (mobile vs. Datacubed web vs. third-party web vs. paper).

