Certain demographic data, such as age (month and year of birth only; all subjects are under 90), gender, sex, ethnicity, education level, employment status, annual income level, and type of smartphone, will be collected from all participants. These data will be analyzed to see if they are associated with any differences in retention, compliance, and engagement. For security, these data will be encrypted and stored in separate files, which can only be referenced through the anonymous subject ID that is assigned to each participant for the study.

Survey data, including survey responses, number of surveys completed, and dates of survey completed will be collected for all participants. These data will be used to evaluate the study endpoints of participant retention, compliance, and usability.

In addition to the aforementioned data types, for the group assigned to the gamified mobile app, several types of data provided by the phone operating system will be collected:

- **Passive data:** These types of data will be collected even when the participant is not actively using the app. Specifically, the app will record information about the participant's

phone battery percentage, geolocation, number of steps taken, apps installed on the phone, and phone screen on/off times. Participants will be fully informed during the consent process that the app will collect such data. They will be able to disable collection of location and step count data at any time by restricting the app permissions via the phone operating system; Android phone owners will also be able to restrict permissions for data collection on screen time.

- Geolocation is the collection of precise geographical location (latitude and longitude) of a device through a mixture of GPS and WiFi signals. This technology is used by many other apps that provide services based on a user's location, such as navigation, rideshare, banking, dating, and fitness apps. When location permissions are allowed, location data is sent to the app every few minutes. In this study, geolocation data will only be used to develop a data-driven model of participants' daily routines. This model will then be compared with self-reported measures of daily activity to see if geolocation data can serve as a measure of activity and routine. Datacubed Health will not share geolocation data with any other external parties and will destroy this data at the end of the study.

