## **Aim 2: Test whether gamification influences participant retention and compliance**

To test whether gamification influences participant retention and compliance, we will perform one-way ANOVA with Dunnett's test for multiple comparisons to assess retention and compliance between the groups receiving electronic administration on the non-gamified websites and the group receiving electronic administration on the gamified mobile app. Non-parametric alternatives (e.g., Kruskal-Wallis test) may be used in place of ANOVA if the data significantly violate the assumptions for ANOVA. This approach will eliminate the potential confounding effect of electronic administration of surveys on the outcome measures by excluding the group receiving paper-based administration of surveys.

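### Aims 1 and 2 each pose one comparison but are tested by two Dunnett comparisons with no deciding rule, in models that leave out payment schedule

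*Protocol*

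**What the plan says.** Section 2 (Objectives) words each hypothesis as one comparison. Aim 1: "There will be a significant difference in retention and compliance between paper and electronic (web) administration of surveys". Aim 2: "There will be a significant difference in retention and compliance between gamified and non-gamified electronic administration of surveys". Each hypothesis then gives an expected direction and names both websites in brackets.

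Section 11 (Data analysis plan) gives the tests. For Aim 1, "we will perform a one-way analysis of variance (ANOVA) with Dunnett's test for multiple comparisons", the purpose being "to assess retention and compliance between the groups receiving paper-based administration of surveys and the two groups receiving electronic administration on the non-gamified websites". For Aim 2, "we will perform one-way ANOVA with Dunnett's test for multiple comparisons to assess retention and compliance", the comparison being "between the groups receiving electronic administration on the non-gamified websites and the group receiving electronic administration on the gamified mobile app". Each aim therefore uses three arms and produces two comparisons against a common comparator. Both paragraphs allow a non-parametric replacement. The opening paragraph of the same plan says that retention and compliance will be analysed by independent t-tests.

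Payment schedule is in neither model. It enters only in the two-way ANOVA for Aim 4, where an arm-by-payment interaction is expected. Section 2, Aim 4 also expects a main effect: "Participants who receive payment at study end will show reduced retention and compliance". Section 9 describes about 100 participants per arm, in a first and a second payment cohort of 50 each.

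The protocol gives no alpha, power, SD or effect size for these aims.

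**The concern.** Retention and compliance are primary outcomes in Section 8. For each, the protocol states one question, names a procedure that returns an overall F and two pairwise results, and elsewhere names a different procedure. It does not say whether the aim is met by the F test, by one Dunnett comparison or by both. If paper differs from one website and not from the other, readers could report the aim as met or as not met, and the protocol would support either.

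Power is also at stake. Splitting a pooled question into two comparisons uses one website group at a time and pays a multiplicity penalty. If the websites perform alike, that makes the stated hypothesis harder to confirm.

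Payment is a separate and smaller matter. The protocol builds it into the design and predicts that it will move both outcomes and change the size of the arm differences. A one-way model leaves that effect in the residual and reports an unstated average over two payment regimes.

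**Working it through.** The protocol states no detectable difference, so there is no figure of its own to reproduce.

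**Inputs**
- From the protocol: about 100 per arm (Section 9). The pooled contrast is 100 against 200 and each Dunnett comparison is 100 against 100. Payment is split about 50:50 within each arm.
- Assumed: two-sided 0.05 (familywise within Dunnett), 80% power with 90% as a check, and both websites equally far from the comparator unless stated otherwise. Differences are in within-arm SD units; the ratios do not depend on the SD.

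**Step 1. Standard errors and critical values (three arms, 297 df)**
- Contrast: SE = sqrt(1/100 + 1/200) = 0.1225; critical t = 1.968.
- One Dunnett comparison: SE = sqrt(2/100) = 0.1414; critical value = 2.223 (two comparisons, correlation 0.5).

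**Step 2. Detectable difference, (critical value + 0.842) × SE**
- Contrast: (1.968 + 0.842) × 0.1225 = 0.344.
- One given Dunnett comparison: (2.223 + 0.842) × 0.1414 = 0.433; the noncentral t gives 0.434.
- Ratio: 0.434 / 0.344 = 1.26. At 90% power, 0.496 / 0.398 = 1.25.

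The 26% has two sources. The smaller comparison group gives sqrt(0.02/0.015) = 1.155. The Dunnett critical value gives 3.065/2.810 = 1.091. Their product is 1.26, so the omitted payment term contributes nothing to it.

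**Step 3. Other rules for success.** The F test uses the noncentral F; the either and both rules were simulated.

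| Rule that decides the aim | Detectable difference, 80% power | Relative to contrast | Power at 0.344 SD |
|---|---|---|---|
| Pooled contrast | 0.344 SD | – | 80% |
| Either Dunnett comparison | 0.367 SD | +7% | 75% |
| Omnibus F | 0.382 SD | +11% | 71% |
| One given Dunnett comparison | 0.434 SD | +26% | 58% |
| Both Dunnett comparisons | 0.479 SD | +39% | 42% |

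**Step 4. Websites that differ.** Suppose, as an assumption, that one website is 0.35 SD from paper and the other 0.15 SD.
- The pooled effect is (0.35 + 0.15)/2 = 0.25 SD. Contrast power is Φ(0.25/0.1225 − 1.96) = Φ(0.08), about 53%.
- Dunnett power for the better website is Φ(0.35/0.1414 − 2.22) = Φ(0.25), about 60%. For either website it is about 61% by simulation.
- With both websites at 0.35 SD the figures are 81% for the contrast, 60% for one given comparison, 76% for either and 44% for both.

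**Step 5. Leaving out payment.** A 50:50 factor that shifts the outcome by p SD adds p²/4 to the residual variance, so the residual SD is multiplied by sqrt(1 + p²/4).
- p = 0.2: sqrt(1.01) = 1.005, or 0.5%.
- p = 0.5: sqrt(1.0625) = 1.031, or 3%.
- p = 0.8: sqrt(1.16) = 1.077, or 8%.

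These values of p are assumed. Because the split is about equal in every arm, the arm contrast is not biased.

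**The case against.** Testing each website separately is a defensible choice. The hypotheses name both websites, and Dunnett against a common comparator fits that reading. A split result is informative, because it shows which platform differs. The protocol does not treat the platforms as interchangeable: Aim 3 orders them on usability. Where they differ enough, the contrast is the weaker test, as Step 4 shows. All of this stands, and it is why the Dunnett comparisons should be kept.

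Payment is also analysed for the same outcomes under Aim 4, so its absence from Aims 1 and 2 is a modest inefficiency. That stands too.

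It can further be said that decision rules and covariates belong in the statistical analysis plan, which is not at hand. For covariates this is fair: Section 9 says of the demographics "These data will be analyzed to see if they are associated with any differences in retention, compliance, and engagement", and leaving them out of these models is no error. It does not dispose of the main point, because the protocol itself names two different procedures for the same outcomes, and neither is tied to the hypothesis.

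On Aim 3, a reader might infer that Tukey's procedure cannot deliver the web-versions comparisons listed in Section 11. The text does not settle that. The phrase can mean each website in turn, which pairwise Tukey covers, and the method behind it extends to general contrasts in balanced designs.

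**Conclusion.** The mismatch holds. Single-comparison hypotheses, t-tests and a one-way ANOVA with two Dunnett comparisons stand side by side for the same primary outcomes, with no rule for which result decides the aim. If the websites perform alike, every reading of the Dunnett or F route is less sensitive than the matching contrast, by 7% to 39% in detectable difference. This rests on assumed two-sided 0.05, 80% power and 100 per arm.

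A reader might infer that the plan costs these aims a quarter of their sensitivity, and that ignoring payment is part of that cost. Neither follows. The 26% belongs to one given comparison, comes entirely from the split, and gives way to a contrast disadvantage if the websites differ enough. Omitting payment is a separate matter: it does not bias the arm contrast and costs 0.5% to 3% in residual SD for assumed effects of 0.2 to 0.5 SD, or 8% at 0.8 SD. The case for including it is that the protocol predicts an interaction, so the average over schedules should be explicit. The change is worth making because it costs nothing, although the existing analysis is not invalid.

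**What to change.** In Section 11:
- For retention and compliance, use the format-by-payment model already planned for Aim 4.
- Make the primary test of Aim 1 the contrast of paper with the mean of the two websites, and of Aim 2 the contrast of the app with the mean of the two websites, both averaged over payment schedule. State that these contrasts decide the aims.
- Keep the single-website Dunnett comparisons as secondary, so that a difference between platforms remains visible.
- Retain a rank-based or other robust fallback, since both outcomes are bounded.
- Reconcile the t-test sentence in the opening paragraph with the paragraphs for Aims 1 and 2.
- For Aim 3, add the two pooled-web contrasts if the websites are meant as a pair.

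Adjustment for the collected baseline variables is optional. The cost is wording only; no new data or participants are needed.

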## **Aim 2: Test whether gamification influences participant retention and compliance**

To test whether gamification influences participant retention and compliance, we will perform one-way ANOVA with Dunnett's test for multiple comparisons to assess retention and compliance between the groups receiving electronic administration on the non-gamified websites and the group receiving electronic administration on the gamified mobile app. Non-parametric alternatives (e.g., Kruskal-Wallis test) may be used in place of ANOVA if the data significantly violate the assumptions for ANOVA. This approach will eliminate the potential confounding effect of electronic administration of surveys on the outcome measures by excluding the group receiving paper-based administration of surveys.

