Each participant will be informed immediately of their group assignment and compensation scheme. Participants who are assigned to the mobile app group will receive additional instructions on how to download and log into the app. Participants who are assigned to the Datacubed Health website group will receive an email with instructions and a link to log into the Datacubed Health web portal. Participants who are assigned to the third-party website (Qualtrics) will be informed that they should expect to receive an email with a custom link to complete surveys each week. The third-party website will not be provided with any participant information, including email addresses. Subjects will only be identified to the third-party website with unique, randomly generated alphanumeric IDs. A script hosted by Datacubed Health will link these IDs to participant email addresses, internally. A master list of alphanumeric subject IDs and participant email addresses will be visible only to study administrative staff at Datacubed Health. Participants who are assigned to the paper group will be informed that they should expect to start receiving their surveys by mail each week.

Participants in all groups will be assigned the same set of study instruments, in the same order. See separate attachments for a listing and full text of all planned survey instruments. Each instrument will take no more than 10 minutes to complete (including embedded instructions), but most will be substantially shorter (2-3 minutes).

Participants in the gamified mobile app condition must log into the mobile app and will see a rich user interface - this includes a customizable avatar, progress-tracking maps that are gradually revealed as study activities are completed, points earned by completing study activities that can be redeemed for virtual avatar accessories (e.g. a hat or sunglasses), and other appealingly designed features (e.g. animated confetti displayed when study activities are completed). Participants in the non-gamified web conditions (Datacubed Health and third-party) must log into the respective web platform and will simply see a scrollable list of available study activities. Participants in the paper condition will be mailed paper surveys, which they must return to the study team through mail using pre-addressed and stamped envelopes. Screenshots illustrating examples of each study condition are provided as a separate attachment.

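### Aim 2 credits gamification alone with a difference that also contains smartphone-app delivery and app-only data collection; the four arms cannot separate them

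*Protocol*

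**What the plan says.** Section 2 of the protocol titles Aim 2 as a test of whether gamification influences retention and compliance, and hypothesises: "Gamification will improve retention and compliance, such that administration on the gamified app will have higher retention and compliance". The comparators are the two non-gamified websites. Section 11 plans a one-way ANOVA with Dunnett's test on Arms A, B and D and makes one statement about confounding for this aim: "This approach will eliminate the potential confounding effect of electronic administration of surveys on the outcome measures by excluding the group receiving paper-based administration".

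Section 9 describes the conditions. For Arm A: "Participants in the gamified mobile app condition must log into the mobile app and will see a rich user interface". Participants in Arms B and D "must log into the respective web platform and will simply see a scrollable list of available study activities". Section 9 also describes collection for Arm A that it gives for no other arm: "for the group assigned to the gamified mobile app, several types of data provided by the phone operating system will be collected". This covers battery level, geolocation, steps, installed apps and screen on/off times, and it runs when the app is not in use.

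Aim 5 (Sections 2 and 11) is likewise titled as a test of gamification and compares app with web delivery of cognitive tasks.

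**The concern.** The title and lead clause of Aim 2 name gamification as the cause, and the only remark on confounding suggests that the contrast has been cleaned up. Yet both sides of the Aim 2 contrast are electronic, so paper versus electronic was never the difficulty within it. The open question is app versus browser, and dropping the paper arm leaves that untouched.

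Gamification is part of the primary objective, and Section 3 says the study will fill a gap in evidence on gamifying a smartphone data collection system. A positive result could come from having an app on the phone. A null result could come from installation or tracking burden masking a real benefit. In either case a conclusion about gamification as such would go beyond what the arms can support.

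**Working it through.** **1. Layout of the electronic arms** (Section 2 table; Section 9, Arms A-D)

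| | Gamified | Not gamified |
|---|---|---|
| Smartphone app | Arm A | none |
| Browser | none | Arms B, D |

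Two of the four cells are empty. Arm C is paper and not gamified.

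**2. What can be estimated.** Let *g* be the effect of gamification and *a* the effect of app rather than browser delivery, including everything else found only in the app arm. Leaving aside any difference between the two websites:

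- mean of Arm A = m + g + a
- mean of Arms B and D = m
- A − B = A − D = g + a

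The indicators for gamified and for app are both 1 in Arm A and 0 in B and D. They are the same column, so only the sum g + a is estimable. B versus D compares two non-gamified websites and says nothing about *a*. Adding Arm C brings in a separate paper mean and again says nothing about *a*. Covariates or a larger sample do not change this.

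**3. What is inside *a*, as documented**

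- Medium: an app on the participant's own phone, against a browser that may be on a computer, tablet or phone (Section 4).
- Set-up: Arm A must download and log into an app (Section 9).
- Passive collection: described for the app group only (Section 9).
- Login: Section 11 offers the app group fingerprint or face login and gives the web groups an ID code and password.

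These could act in opposite directions, so the sign of *a* is unknown.

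**4. The confounding sentence.** After Arm C is dropped, all remaining arms are electronic. Paper versus electronic is therefore constant across the contrast, and in that sense the sentence is right. App versus browser still differs between Arm A and its comparators, so the exclusion does not isolate *g*.

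**5. Illustration of size.** The protocol gives no alpha, SD or effect size for this aim, so there is no figure to reproduce. Assumptions: two-sided alpha 0.05, normal outcome, n = 100 per arm, g = 0, and *a* set to values from 0 to 0.5 SD against both websites.

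- Standard error of a contrast in SD units: √(2/100) = 0.141.
- Dunnett critical value, two comparisons, 3 × 100 − 3 = 297 df, by simulation: 2.21.
- One contrast at a = 0.2: 0.2/0.141 = 1.41; P(Z > 2.21 − 1.41) ≈ 0.21.
- One contrast at a = 0.3: 0.3/0.141 = 2.12; P(Z > 2.21 − 2.12) ≈ 0.46.
- At least one of two = 2 × (one) − (both). Simulated values at 0.2: 2 × 0.213 − 0.096 = 0.33. At 0.3: 2 × 0.464 − 0.297 = 0.63.

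| Assumed a (SD) | 0 | 0.1 | 0.2 | 0.3 | 0.4 | 0.5 |
|---|---|---|---|---|---|---|
| Any Aim 2 contrast significant | 5% | 12% | 33% | 63% | 87% | 97% |

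**6. Aim 5.** One follow-up arm is a gamified app and the other a non-gamified website, so again only g + a is estimable. At the maximum of 200 per arm the standard error is √(2/200) = 0.1. A shift of 0.2 SD gives P(Z > 1.96 − 2.0) ≈ 52%, and 0.3 SD gives P(Z > 1.96 − 3.0) ≈ 85%, on the same kind of assumption.

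**The case against.** The strongest reply is that the package is already disclosed. The Section 2 table shows app and gamification together, and the second half of the Aim 2 hypothesis spells out the comparison: "administration on the gamified app will have higher retention and compliance compared to administration on the non-gamified websites". On that reading only a heading and a lead-in use too short a word, and the comparison itself is valid. This is right about the comparison and about the size of the edit. It does not rescue the attribution, because the title and the causal clause still name gamification and nothing in Section 11 qualifies them.

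A reader might infer that the protocol claims to have removed all confounding. It does not. The sentence names one effect, electronic administration, and on that narrow point it is true. It is incomplete rather than false.

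A reader might also infer that unequal weekly prompts bias the contrasts. Section 9 says Arm D participants "will be informed that they should expect to receive an email with a custom link to complete surveys each week", while Arm B participants "will receive an email with instructions and a link to log into the Datacubed Health web portal". The second reads as an onboarding message, and the first is how Arm D's surveys are delivered. The protocol does not say whether Arms A and B receive recurring notices, and silence does not establish an imbalance. If Arm A had none, the imbalance would work against the Aim 2 hypothesis.

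The burden of passive collection is also uncertain. Participants can switch off location and step collection, and disclosure takes place at consent, before assignment. That leaves the size and sign of *a* open; it does not make *a* estimable.

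**Conclusion.** The concern holds for attribution. An Aim 2 difference supports a statement about the gamified app as a package against a non-gamified website, and nothing narrower. The share due to gamification is not identified: if the observed difference were 0.3 SD, an assumed app effect between 0 and 0.3 SD would put the gamification effect anywhere from 0.3 SD down to 0, and a negative app effect would put it above 0.3 SD. This follows from the arm structure alone and needs no distributional assumption.

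The 33% and 63% figures are illustrations under assumed shifts. They show how readily the planned test would pick up an app effect of that size, not that one exists.

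It would be tempting to carry the whole point over to Aim 5. Only the app-versus-web aliasing carries over. The confounding sentence is not made for Aim 5, passive collection is not described for the follow-up, the hypothesis already mentions a mobile device beside the gamified format, and Section 11 labels the contrast as app against web. There the title and the permitted conclusion need narrowing.

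**What to change.** - **Aim 2, Sections 2 and 11:** restate the title, hypothesis and permitted conclusion as gamified smartphone app (including its passive data collection) versus non-gamified website.
- **Section 11, Aim 2:** limit the confounding sentence to paper versus electronic, and add that app versus browser remains, so an Aim 2 difference cannot be attributed to gamification alone.
- **Aim 5, Sections 2 and 11:** make the same change to the title and conclusion, as gamified app versus non-gamified web tasks.

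The cost is wording only. Arms, sample size and tests are unchanged, but the headline claim becomes narrower. A weekly email to all four arms should not be added on this ground: an imbalance in prompts is not established, and an electronic notice to the paper arm would change the paper condition that Aim 1 compares with the websites.
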